## 7.8 Administration of intervention

Following baseline data collection the participant will be granted access to either the trial intervention or control intervention. Access to the Oto app will be immediate. The first face-to-face CBT appointment will be scheduled within +/- 1 week.

## 7.9 GP contact and hearing test referral

With the participant’s permission provided on the trial consent form, a letter will be sent to the participant’s GP to inform them that the individual has entered the DEFINE trial.

It will be recommended to all participants both on the screening phone call and in the following email that they speak to their GP and request referral for a formal pure tone audiogram hearing test. The method of referral will be at the discretion of the GP, but it will be recommended that this is achieved via referral to an approved high street provider under the Any Qualified Provider (AQP) scheme.

## 7.10 Follow-up (remote)

### 7.10.1 Month 1 (Study week 4 +/- 7 days)

To collect data to include but not limited to:

- Complete TFI questionnaire
- Adverse events
- Any change in medication (particularly medications known to be associated with tinnitus, e.g. Aspirin, diuretics) or introduction of hearing aid

### 7.10.2 Month 3 (Study week 12 +/- 14 days)

To collect data to include but not limited to:

- Complete TFI questionnaire
- Complete EQ-5D-5L and HUI3 questionnaires
- Adverse events
- Complete System Usability Score (SUS)
- Complete questionnaire on primary and community healthcare appointments and A&E visits related to tinnitus since week 4
- Complete questionnaire on personal out-of-pocket tinnitus related costs, any time-off work and travel information to appointments incurred since week 4
- Any change in medication (particularly medications known to be associated with tinnitus, e.g. Aspirin, diuretics) or introduction of hearing aid

### 7.10.3 Month 6 (Study week 26 +/- 14 days)

To collect data to include but not limited to:

- Complete TFI questionnaire
- Complete EQ-5D-5L and HUI3 questionnaires
- Complete questionnaire on primary and community healthcare appointments and A&E visits related to tinnitus since week 12
- Complete questionnaire on personal out-of-pocket tinnitus related costs, any time-off work and travel information to appointments incurred since week 12
- Any change in medication (particularly medications known to be associated with tinnitus, e.g. Aspirin, diuretics) or introduction of hearing aid

### 7.10.4 Month 12 (Study week 52 +/- 28 days)

To collect data to include but not limited to:

- Complete TFI questionnaire
- Complete EQ-5D-5L and HUI3 questionnaires
- Complete questionnaire on primary and community healthcare appointments and A&E visits related to tinnitus since week 26
- Complete questionnaire on personal out-of-pocket tinnitus related costs, any time-off work and travel information to appointments incurred since week 26
- Any change in medication (particularly medications known to be associated with tinnitus, e.g. Aspirin, diuretics) or introduction of hearing aid

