# 11. HEALTH ECONOMIC EVALUATION

## 11.1 Health Economic Evaluation

A health economic evaluation forms an integral part of the trial and will be conducted from the perspectives of the NHS, personal and the society. The economic evaluation will take the form of a cost-utility analysis with a one-year time horizon using quality-adjusted life years (QALYs) as the main outcome measure. Although the clinical study has a non-inferiority design and our hypothesis is that QALYs will be similar between the Oto app and standard care, there is no prior hypothesis that costs will be similar between groups. Therefore, a standard economic evaluation framework will be used to synthesise differences in costs and QALYs between study arms using the incremental cost-effectiveness ratio (ICER)^8^.

We will follow all participants from baseline to 12 months and will collect information about the delivery of the intervention (app and standard care), primary and community health care, visits to accident and emergency (A&E) and prescribed medications. We will focus on the collection of resource utilisation related to tinnitus. Data will be collected using bespoke questionnaires that will be embedded into the Lindus Health EDC platform for participant completion at regular intervals during follow-up (weeks 12, 26 and 52). Unit costs from recognised national sources including the new NHS National Cost Collection, the Personal and Social Services Research Unit (PSSRU), and the NHS Electronic Drug Tariff will be used to value NHS health care resource use. To understand the burden beyond the health service, we will ask participants about any related out-of-pocket expenses (e.g. hearing aids, complementary and alternative paid treatments) and any time away from paid employment due to the condition.

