# 23. APPENDIX 2 - SCHEDULE OF EVENTS TABLE

| **Procedure** | **Pre-screener**  Week -*N* | **Screening**  Week 1, Day 0 | **Randomisation**  Day 0 | **Baseline**  Week 1, Day 1 (+ 7 days) | **Oto App starts for 6wks / consultation for CBT booked**    Day 1 | **Month 1 Follow Up**  Week 4, Day 1 (+/- 7 days) | **Month 3 Follow Up**  Week 12, Day 1 (+/- 14 days) | **Month 6 Follow Up**  Week 24, Day 1 (+/- 14 days) | **Month 12 Follow Up**  Week 52, Day 1 (+/- 28 days) |
| --- | --- | --- | --- | --- | --- | --- | --- | --- | --- |
| Informed Consent | ✓ | ✓ |  |  |  |  |  |  |  |
| Eligibility assessment | ✓ | ✓ |  |  |  |  |  |  |  |
| Medical history | ✓ | ✓ |  |  |  |  |  |  |  |
| Demographics |  | ✓ |  |  |  |  |  |  |  |
| Tinnitus Background Survey |  |  |  | ✓ |  |  |  |  |  |
| Tinnitus Functional Index (TFI) |  |  |  | ✓ |  | ✓ | ✓ | ✓ | ✓ |
| EQ-5D-5L |  |  |  | ✓ |  |  | ✓ | ✓ | ✓ |
| HUI3 |  |  |  | ✓ |  |  | ✓ | ✓ | ✓ |
| Resource Use Questionnaire |  |  |  |  |  | ✓ | ✓ | ✓ | ✓ |
| System Usability Scale |  |  |  |  |  |  | ✓ |  |  |
| AE review |  |  |  | ✓ |  | ✓ | ✓ |  |  |
| Study Experience Questionnaire |  |  |  |  |  |  | ✓ | ✓ | ✓ |
| Adherence Data collected (eCRF) |  |  |  |  |  | ✓ | ✓ | ✓ | ✓ |

#

#

#

#

#

#

#

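### Resource-use recall starts at fixed weeks although the forms have completion windows: as worded, recall periods can leave gaps or overlap, and the last need not end at one year

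*Protocol*

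**What the plan says.** The Month 3 list in section 7.10.2 of the protocol has the item "Complete questionnaire on primary and community healthcare appointments and A&E visits related to tinnitus since week 4". Section 7.10.3 (Month 6) has "Complete questionnaire on primary and community healthcare appointments and A&E visits related to tinnitus since week 12", and section 7.10.4 (Month 12) has "Complete questionnaire on primary and community healthcare appointments and A&E visits related to tinnitus since week 26". A companion item in each section covers out-of-pocket costs, time off work and travel, with the same start week.

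The section headings set the completion windows: "Month 1 (Study week 4 +/- 7 days", "Month 3 (Study week 12 +/- 14 days", "Month 6 (Study week 26 +/- 14 days", and for Month 12, week 52 with 28 days either side. Section 10.4 treats a patient-reported form as missing only when it falls outside its window, so a form completed anywhere inside the window is accepted.

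Section 11.1 describes a "cost-utility analysis with a one-year time horizon using quality-adjusted life years" and collects resource use at weeks 12, 26 and 52. Neither 7.10 nor 11.1 ties the start of a recall period to the date of the previous form.

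Appendix 2 differs in two respects. It places Month 6 at "Week 24, Day 1 (+/- 14 days", and it ticks a resource-use questionnaire at Month 1, which sections 7.10.1 and 11.1 do not list.

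**The concern.** Each recall period begins at a nominal week and ends on the day the form is filled in. Two consecutive periods meet exactly only when the earlier form is completed on its nominal day. If that form is early, the days up to the next fixed start fall in no form. If it is late, the days after the fixed start fall in two forms. The last period ends wherever the Month 12 form is completed, which need not be one year.

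At stake are the participant-reported costs in the cost-utility analysis, a listed secondary outcome. A participant's recorded visits, expenses and work loss would depend partly on when the forms were returned. Events that no form asked about cannot be restored by any analysis plan, and events reported twice can be removed only if they are dated, which the protocol does not say.

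**Working it through.** **Inputs.** Start weeks 4, 12 and 26 (sections 7.10.2 to 7.10.4). Completion weeks 12 + d1, 26 + d2 and 52 + d3, with d1 and d2 between -2 and +2 weeks and d3 between -4 and +4 weeks (the same headings). Horizon: one year (section 11.1).

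**1. Nominal dates.** (12 - 4) + (26 - 12) + (52 - 26) = 8 + 14 + 26 = 48 weeks, with no gap or overlap. Adding weeks 0 to 4 gives 52, so the one-year horizon is reached only if the Month 1 form ticked in Appendix 2 is collected and used.

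**2. Boundaries at weeks 12 and 26.** The gap is the start week minus the previous completion week (early form); the overlap is the reverse (late form). The maximum is 2 weeks at each. For example, with Month 3 completed at week 14, an A&E visit in week 13 belongs to both the Month 3 and the Month 6 recall. With Month 3 completed at week 10, weeks 10 to 12 belong to neither. If a Month 1 form exists, week 4 adds a gap or overlap of up to 1 week.

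**3. Last form.** Its recall runs from 48 - 26 = 22 to 56 - 26 = 30 weeks, against 26 nominal (85% to 115%).

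**4. Total from week 4.** Weeks counted = 48 + d1 + d2 + d3.
- All three forms at the late limit: 56 weeks (+8/48 = +16.7%), of which 4 are counted twice and 4 lie beyond week 52.
- All three at the early limit: 40 weeks (-16.7%), with 4 weeks in gaps and 4 uncovered before week 52.
- With a Month 1 form included, the range is 43 to 61 weeks against 52.

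**5. Less extreme completion patterns (all assumptions; the protocol gives no timing data).**
- Uniform over the full windows: mean error 0. Each boundary averages 0.5 weeks lost and 0.5 weeks double-counted, so 1 week of each per participant over the two. The SD of the total is √(4²/12 + 4²/12 + 8²/12) = √8 = 2.8 weeks; the simulated 95% range is about -11% to +11%.
- Uniform over the late half of each window: mean excess 1 + 1 + 2 = 4 weeks, or 52/48 = +8.3%.
- Uniform over 0 to 4 days late: mean excess 3 × 2 = 6 days in 336, or 1.8%; maximum 12/336 = 3.6%.

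**6. Appendix 2 schedule.** Month 6 at week 24 with 14 days either side falls in weeks 22 to 26. The Month 12 recall still starts at week 26, so the gap is 0 to 4 weeks (mean 2 under uniform completion) and there is never an overlap there. Even at nominal dates the sum is 8 + 12 + 26 = 46 weeks, against 48. This is a systematic loss and does not average out.

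**The case against.** The strongest reply is that section 7.10 is a list of data items, not the questionnaire text. The instruments are bespoke forms in the data-capture platform and are not shown. A start week may be shorthand for the previous contact, and the live form may display a date. This stands: the effect follows only if the forms carry the protocol's wording.

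Cutting or scaling costs to one year may also be left to an analysis plan that is not shown, so its absence from the protocol is not itself the fault. The recall start is different, because it is a data-collection rule that the protocol states.

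A reader might infer that late returns inflate costs by 8% to 17%. The documents do not support that. The 16.7% figure needs all three forms at the same window limit. Section 7.1 provides weekday review, an alert, daily reminders for 3 days and then direct contact, which sits badly with returns spread evenly across the late half of every window.

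A reader might also infer a biased incremental cost. The windows are the same in both arms, and nothing in the protocol shows that promptness differs between them. Nor are the percentages shares of total cost: they are shares of recall time for participant-reported items. Delivery of the app and therapy is recorded separately (sections 8.2 and 11.1) and is unaffected.

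**Conclusion.** The point holds conditionally. If the forms use the section 7.10 wording, up to 2 weeks at each of the week 12 and week 26 boundaries are missed or asked about twice, and the last recall ends between weeks 48 and 56. Recall time from week 4 can then be anything from 40 to 56 weeks against 48. If completion centres on the section 7.10 dates the mean error is zero, and the harm is noise in individual participants' reported costs. An equal shift in both arms does not create a difference between them; bias in favour of an arm requires promptness to differ by arm, which is possible in an unblinded trial but not shown.

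The exception is the Appendix 2 schedule, under which the loss before week 26 runs one way. Sections 7.10.3 and Appendix 2 must be reconciled whatever the forms say. The correction is worth making because it is cheap and because missed events cannot be recovered later.

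**What to change.** 1. In sections 7.10.2 to 7.10.4, replace the fixed start weeks with the date of the participant's last completed resource-use questionnaire, displayed by the data-capture system. Apply this to both the healthcare-use item and the item on out-of-pocket costs, time off work and travel. If the live forms already do this, amend the protocol text to say so.
2. Reconcile sections 7.10.1 and 11.1 with Appendix 2 on whether a Month 1 resource-use form is collected. If it is not, anchor the first form to baseline/randomisation; otherwise the new wording has no referent at Month 3 and weeks 0 to 4 stay uncovered.
3. Reconcile section 7.10.3 with Appendix 2 on the week of the Month 6 contact.
4. State that where a form was missed, the next form covers the missed period and that period is not also imputed. Without this, the multiple imputation allowed in section 11.1 could count it twice.
5. In section 11.1 or the analysis plan, use completion dates to bring the last form's costs to one year. With step 1 in place, gaps and overlaps vanish and the total span is the time to the last form, 48 to 56 weeks (92% to 108% of 52). Cutting works for a late form with dated entries; scaling is needed for an early one.
6. For forms already returned, adjust for actual recall length from completion dates, and report that events falling in gaps cannot be recovered.

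The cost is a text change in the data-capture system that displays a stored date, plus short edits to sections 7.10 and 11.1 and Appendix 2. It needs no extra visits, staff or participants.

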## 7.11 Early Discontinuation/Withdrawal of Participants

Each participant has the right to withdraw from the study at any time. In addition, the participant’s GP or trial Sponsor may discontinue the participation of a participant from the study at any time, if this is considered necessary for any reason including:

● Pregnancy

● Ineligibility

- Participant decision

● Inability to comply with study procedures

● Withdrawal of consent

Following participant withdrawal, no further clinical assessments will be performed. The participant will be contacted by a member of the central team and a reason for withdrawal will be requested and documented. All data recorded prior to withdrawal will be analysed in the intention-to-treat population.

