## 7.1 Digital Applications

For the duration of the trial participants will be asked to record their responses to questionnaires directly into the Lindus Health Electronic Data Capture (EDC) platform, via a participant survey link, which will be emailed and/or texted to them. The participants in the smartphone delivered CBT arm will also use the Oto tinnitus app. Certain fields may require duplicate data entry between the two digital systems, but it is essential that data on the Lindus Health platform is completed fully.

The Lindus Health team will have access to the EDC data and will review this on a daily basis (excluding weekends). Missing data will trigger an alert message to the participant via text/email. If no response is entered, a daily reminder will be triggered for 3 days, after which point the Lindus Health team will contact the participant to assess if they wish to withdraw from the study. If a participant wishes to withdraw then they will be advised to arrange an appointment with their GP or healthcare provider to discuss other treatment options (i.e. return to standard care), and a reason for withdrawal will be documented. Free access to the app will continue for participants in the Oto arm, or be offered free for 12 months from completion of the study for participants in the control group.

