## 9.4 SAE Reporting

Any AEs which fall under the definition of a SAE will be reported to the Chief Investigator or designated person within 24 hours, to be reviewed for relatedness and expectedness. However, hospitalisations for elective treatment of a pre-existing condition do not need reporting as SAEs.

Reports of related and unexpected SAEs (in the opinion of the Chief Investigator or designated person) will be reported to the REC within 15 days of the CI and/or central trial team becoming aware of the event. The Chief Investigator will also notify the Sponsor of all study SAEs.

Any pregnancy occurring during the study will result in the immediate discontinuation of the participant and the Sponsor should be notified within 24 hours so appropriate follow-up is conducted. Pregnancy itself is not an AE.

All SAEs will be recorded in the Citrus platform and any concerns raised immediately with the CI and may be tabled for discussion at the regular Trial Management Group meeting or referred to an independent Trial Steering Committee (TSC) for review.

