## 10.1 Description of Statistical Methods

The primary analysis will be conducted on the intention-to-treat (ITT) population. In addition to this, a per-protocol analysis will also be planned as a sensitivity analysis. Compliance will be defined as a minimum of 60 minutes of total use for the intervention group, and one or more sessions for the CBT group. Participants reporting poor compliance will be recorded and these participants will be included in the ITT analysis. Adherence to the smartphone app delivered programme will be monitored through the app with results analysed by intention-to-treat (ITT).

The primary outcome will be reduction in total TFI score at the 6 month point in the ITT population. Non-inferiority will be assessed by constructing a 95% confidence interval around the mean difference in TFI reduction between the groups, and comparing the -upper bound of the confidence interval to the pre-specified non-inferiority margin.

A secondary analysis of the primary outcome will examine significant differences between the control and intervention group’s TFI score at 6 months using a general linear model or a comparable suitable method, using the stratification variables and other potential confounding variables as covariates.

As a sensitivity analysis, the primary outcome will be analysed using the Per-Protocol (PP) population, which consists of participants complying with the treatment regimen. Compliance will be defined as a minimum of 60 minutes of total use for the intervention group, and one or more sessions of CBT for the control group.

Secondary outcomes will be compared between groups and over time with mixed-effects regression models for repeated measures, using the stratification variables and other potential confounding variables as covariates. Logistic models will be used for binary outcomes, and Gaussian models for continuous outcomes. An interim analysis may be conducted once a sufficient number of participants have completed the 6 month milestone. The results of the interim analysis do not influence the continuation of the trial.

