## 10.4 Handling of Missing and Incomplete Data

The Citrus EDC provides real-time notifications to the trial team to inform them of any missing data to minimise the risk of missing data. For patient reported outcomes, the EDC will notify the study team if assessments are overdue so the study team can follow up and collect these outcomes (the trial team will contact the patient up to 3 times). If a patient reported outcome is not completed within the scheduled window, the data will be considered missing with reasons provided. For clinician reported outcomes the EDC system will flag if an outcome is missing. Missing data will be managed according to Lindus Health SOPs. Missing data will be reported with reasons given where available and imputed using multiple imputation for the ITT population. Depending on the extent of missing values, further investigation may be made into the sensitivity of the analysis results to the method(s) specified.

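### Section 7.11 ends all assessments when the sponsor or GP stops participation, even without withdrawn consent, so month-6 TFI scores that a remote survey could collect are lost

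*Protocol*

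**What the plan says.** Protocol section 7.11 gives every participant the right to withdraw. It adds that the GP or the "trial Sponsor may discontinue the participation of a participant from the study at any time". The listed reasons include pregnancy, ineligibility and "Inability to comply with study procedures", and these stand beside withdrawal of consent as separate items. The consequence is the same for all of them: "Following participant withdrawal, no further clinical assessments will be performed". Only data recorded before that point go into the intention-to-treat population.

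Section 9.4 is firmer on one reason: "Any pregnancy occurring during the study will result in the immediate discontinuation of the participant".

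Section 7.1 sets out what happens when a form is missing. After an alert: "If no response is entered, a daily reminder will be triggered for 3 days". Should the form still be outstanding when those reminders end, the next step is worded as follows: "after which point the Lindus Health team will contact the participant to assess if they wish to withdraw from the study". Section 10.4 describes the same situation differently. The team is notified of an overdue outcome so that it can collect it, may contact the participant up to three times, and treats the outcome as missing only once the scheduled window has passed. Section 7.10.3 sets that window at +/- 14 days for month 6.

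On analysis, section 10.1 states: "The primary analysis will be conducted on the intention-to-treat (ITT) population". Under section 10.4, missing data are to be "imputed using multiple imputation for the ITT population".

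**The concern.** An intention-to-treat analysis needs the month-6 outcome of everyone randomised, including people found ineligible afterwards and people who could not follow the study procedures. Section 7.11 applies one rule to participants who refuse further data collection and to those whose participation someone else has ended. For the second group nothing prevents a survey link from being sent. The programme lasts about six weeks (section 8.1) and the primary TFI is due at month 6, so removal after the programme mostly removes data. Section 7.1 even lets withdrawn Oto participants keep free app access, so a person could still be using the app while no longer being measured.

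The trial is open-label and the grounds for removal are partly discretionary, so the losses may be informative and may differ by arm. In a non-inferiority comparison, a difference of that kind shifts the estimate relative to the margin. Multiple imputation can handle such losses under assumptions, but it cannot replace outcomes that were never requested.

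The conflict over late forms matters for the same reason. Raising withdrawal while the window is still open can turn one late form into the loss of every later assessment.

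**Working it through.** **1. The passages side by side.**
- Who can end participation: participant, GP or sponsor (7.11).
- Is withdrawn consent needed? No. It is one listed reason among several (7.11).
- What follows: no further assessments, with earlier data kept (7.11).
- Provision for remote questionnaires afterwards: none found in 7.1, 7.10, 7.11, 10.1, 10.4 or Appendix 2.
- Mode of the primary outcome: participant survey link (7.1).
- Late form: withdrawal enquiry after an alert and three days of reminders (7.1), against contact to collect, with data missing only after the window (10.4). If the link goes out on the nominal date, which the protocol does not say, about 10 days of the month-6 window would remain at the enquiry.

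**2. The plan's own figure.** Inputs from section 10.2: margin 13, SD 31, α 2.5%, power 90%, 90 per group, 10% attrition, 196 in total. One-sided α is taken from the 95% interval in 10.1. A true difference of 0 is assumed.
- n per group = 2 × 31² × (z_α + z_β)² / 13².
- At 90% power: 2 × 961 × (1.960 + 1.282)² / 169 = 119.5, so 120.
- At 80% power: 2 × 961 × (1.960 + 0.842)² / 169 = 89.3, so 90.

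The stated 90 therefore fits 80% power, not 90%. That is a separate matter. Here it means only that there is no reserve to absorb extra loss.

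**3. Power by proportion missing.** With 98 per group randomised, completers only, power = Φ(13 / (31 × √(2/n)) − 1.96).
- 10% missing (n = 88.2): 79.5%.
- 20% missing (n = 78.4): 74.7%.
- 30% missing (n = 68.6): 69.0%.

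**4. Bias.** Let p be the proportion lost in an arm, and k the points by which those lost are truly worse than their imputed values. Neither is given in the protocol, so both are assumed.
- Net bias towards Oto = p(Oto) × k(Oto) − p(control) × k(control).
- Equal loss and shortfall: 0.10 × 20 − 0.10 × 20 = 0.
- 10% against 5% lost, k = 20 in both arms: 1 point.
- 20% against 10% lost, k = 5 to 20: 0.5 to 2 points.
- 30% against 10% lost, k = 5 to 20: 1 to 4 points.
- With the arms swapped, each figure changes sign and works against Oto.

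**5. Effect on the error rate.** SE = 31 × √(2/90) = 4.62. With the truth at the margin, P(false non-inferiority) = Φ(bias / 4.62 − 1.96).
- Bias 0: Φ(−1.96) = 2.5%.
- Bias 1: Φ(−1.744) = 4.1%.
- Bias 2: Φ(−1.527) = 6.3%.
- Bias 4: Φ(−1.094) = 13.7%.
- Bias −2: Φ(−2.393) = 0.8%.

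For scale, one extra person lost from an arm of 98, with a shortfall of 20 points, moves the estimate by 20/98 = 0.2 points.

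**The case against.** The strongest defence is that the protocol does not treat stopping therapy as leaving the study. A reader might infer from 7.11 that it does, but the documents do not support this. Section 10.1 keeps poor compliers in the intention-to-treat analysis, follow-up runs to month 12 after a programme of about six weeks, and adherence is counted at 3 and 6 months, which presupposes that people who have stopped are still followed. The compliance ground in 7.11 concerns study procedures, and no section removes anyone for low app use, missed sessions or poor response. All of this stands and limits the point to participants whose study participation is ended.

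A reader might also infer that a form three days late leads to withdrawal. It does not. The contact is an enquiry, and 10.4 still allows the form to be completed within the window. What remains is that the two sections give the same contact different purposes.

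The word clinical in 7.11 could be read as leaving questionnaires untouched. That is possible, but no section says so, and a rule that governs the primary outcome should not depend on that reading.

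Finally, the imputation model and sensitivity analyses belong to the SAP, and 10.4 allows for further sensitivity work. That is fair, and no criticism of the imputation is made here. The gap lies in data collection, which an analysis plan cannot repair.

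**Conclusion.** The point holds in a limited form and should be fixed. As written, section 7.11 stops collection of the month-6 TFI from participants removed by the sponsor or GP who have not withdrawn consent to follow-up, although a remote questionnaire could still obtain it. Sections 7.1 and 10.4 need to be aligned on late forms.

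It would go too far to conclude that the rule favours a finding of non-inferiority. The direction depends on between-arm differences that the protocol cannot foresee. The bias is zero if loss and shortfall match, and it may run against Oto. The error rates of 4.1%, 6.3% and 13.7% are illustrations for net biases of 1, 2 and 4 points towards Oto. They rest on assumed losses and shortfalls, the planning SD, 90 analysed per arm and a normal approximation. A 20-point shortfall is large, at about 0.65 of the planning SD (20/31). The documents also do not indicate how many losses would come from sponsor or GP removal, which is the clearly avoidable part. The loss of information is more certain than the bias: any avoidable missing outcome draws on a sample with no reserve.

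**What to change.** - **Section 7.11:** distinguish ending the intervention or active participation from withdrawing consent to data collection. State that everyone randomised is asked for the remaining remote questionnaires, at minimum the TFI, unless they withdraw consent to data collection. Record which of the two occurred, and who initiated it.
- **Section 7.1:** make the contact after the reminders an attempt to retrieve the form within the visit window, consistent with 10.4. A participant who wishes to withdraw can still say so. The window also needs one anchor, because 7.10.3 places month 6 at week 26 and Appendix 2 at week 24.
- **Pregnancy:** section 7.11 says participation may be ended, section 9.4 makes discontinuation immediate, and section 6.1.2 explains the eligibility exclusion by insurance cover. These passages must be reconciled, including whether questionnaire-only follow-up is possible. No view is taken here on the clinical rule.

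The cost is a protocol amendment through the usual sponsor, REC and HRA approvals, plus a few extra reminders. No visits are added, and the rules on who stops the intervention do not change.
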